## Abstract

**Introduction:**

Postoperative nausea and vomiting (PONV) are common adverse events following gynecological laparoscopic surgery. This study aims to evaluate the efficacy of transcutaneous auricular vagus nerve stimulation in reducing the incidence of PONV within 24 h after gynecological laparoscopic surgery.

**Methods and analysis:**

This single-center, prospective, double-blinded, randomized and sham-controlled trial will enroll 200 patients scheduled for gynecological laparoscopic surgery. Participants will be randomized in a 1:1 ratio to either the taVNS group or the sham group. The taVNS group will receive electrical stimulation lasting for 30 min after anesthesia induction. Sham group will not provide stimulation. The primary endpoint is the incidence of PONV within the first 24 h after surgery. Secondary endpoints include the severity of PONV, the usage of rescue antiemetics and 5-point Likert satisfaction scale. Exploratory endpoints include consumption of opioids and heart rate variability within 24 h after surgery.

**Discussion:**

The results of study will provide key evidence on the efficacy and safety of intraoperative taVNS for preventing PONV after gynecologic laparoscopic surgery.

Trial registration: Chinese Clinical Trial Registry (registration No. ChiCTR2600120159; registered on March 10, 2026)

## Introduction

Postoperative nausea and vomiting (PONV) are common adverse events after surgery and anesthesia, with an increased risk of reflux aspiration, suture dehiscence, postoperative bleeding, electrolyte imbalance, prolonged hospital stay and reduced patient satisfaction [1,2]. Independent risk factors most commonly associated with PONV include female sex, non-smoker, history of PONV and postoperative opioids [1,3]. Meanwhile, pneumoperitoneum, use of inhalation anesthetics and intraoperative opioid analgesics also increase the risk of PONV [4]. Patients undergoing gynecological laparoscopic surgery belong to the PONV high-risk population, with the incidence rates of moderate to severe PONV remaining around 30%–40%[4,5].

The underlying neural circuits associated with PONV include input *via* the vagus nerve, neurons in the area postrema, the vestibular system, and potentially other cell types [6,7]. Meanwhile, some exogenous stimuli could induce PONV by releasing emetic neurotransmitters to activate corresponding emetic receptors, such as those for 5-hydroxytryptamine (5-HT), neurokinin-1 (NK-1R), dopamine D2 and D3, mu and kappa opioid, muscarinic M1, and histamine H1 receptors [8,9]. Currently, the prevention of PONV mainly involves antiemetic drug intervention by acting on receptors. However, most of the antiemetics can have adverse effects and the effectiveness can be inconsistent among patients [10]. The multiple therapeutic approaches of PONV should be explored.

Transcutaneous auricular vagus nerve stimulation (taVNS) is an emerging neuromodulatory technique, which has been explored to regulate central and peripheral organs function [11–13]. The external ear is the only place on the body where VN sends its peripheral branch [14,15]. The stimulation on the auricular branch of the vagus nerve (ABVN) could connect directly to the brainstem, and then to higher brain regions *via* extensive projections to second and third order neurons within the brain [16,17]. Consequently, given that taVNS involves both sympathetic and parasympathetic branches, it generates systemic effect. It is reported taVNS regulates the gastrointestinal tract in rats with functional dyspepsia by increasing the gastric emptying rate improving gastric motility, reducing gastric sensitivity, and alleviating low-grade inflammation [18]. Moreover, more researchers focus on the effect of taVNS on postoperative pain management or perioperative anxiety [19,20]. However, there is limited research on impact of taVNS on PONV.

Therefore, this double-blind randomized controlled trial will be designed to investigate the effect of the taVNS on the incidence of PONV within 24 h after surgery in female patients undergoing elective gynecologic laparoscopic surgery under general anesthesia. As a secondary aim, we plan to assess the effects of taVNS on the severity of postoperative nausea, the dosage of antiemetic drugs administered, and patient satisfaction.

## Patients and methods

### Study design and registration

This study is a single-center, prospective, double-blinded, randomized and sham-controlled clinical trial. The trial has been approved by the Ethics Committee of the First Affiliated Hospital of Soochow University (Approval no.2025-1298) and registered at clinical trials.gov (registration No. ChiCTR2600120159). The trial is conducted in accordance with the Declaration of Helsinki and will be monitored by the clinical trial center of the hospital. Written informed consent will be obtained from each patient before randomization and surgery. The SPIRIT checklist is included in supplemental file S1. The trial flow diagram is shown in Figure 1. Schedule of subject enrollment, interventions, and outcome measurements are presented in Table 1.

**Figure 1. F0001:**
[figure not shown]
Flow diagram of this trial. taVNS: transcutaneous auricular vagus nerve stimulation; ITT: intention-to-treat; PP, per-protocol.

**Table 1. t0001:** Schedule of subject enrollment, interventions, and outcome measurements.

	Study period							
	Enrollment	Allocation	Post-allocation					Close-out
TIMEPOINT	Preanaesthesia visit	preoperative	Intraoperative	1 h	2 h	6 h	12 h	24 h
**Enrollment**	x							
Eligibility screen	x							
Informed consent	x							
Baseline assessment	x							
Randomization		x						
**Inventions**								
The taVNS group			x					
The sham group			x					
**Assessments**								
Nausea				x	x	x	x	x
Vomiting				x	x	x	x	x
NRS				x	x	x	x	x
Rescue antiemetics								x
5-point Likert scale								x
Consumption of opioids								x
Heart rate variability		x	x					x
Adverse events			x	x	x	x	x	x

taVNS: transcutaneous auricular vagus nerve stimulation; NRS: numerical rating scale.

### Study population

Patients scheduled for gynecological laparoscopic surgery in the First Affiliated Hospital of Soochow University will be recruited for the research. Patients will be eligible for participation if they are aged from 18 to 65 and have an American Society of Anesthesiologists physical status of class I to II. Exclusion criteria include: (1) infection, malformation or injury in the outer ear; (2) administration of antiemetic drugs, glucocorticoids or opioids within 24 h preoperatively; (3) neurologic, or cognitive dysfunction, or psychological disorders; (4) pregnancy or breastfeeding; (5) refusing to provide informed consent.

The preparatory phase of this study (including staff training, equipment calibration and finalization of standard operating procedures) commenced on January 24, 2026 and the first participant was enrolled on March 16, 2026, which was shortly after the completion of trial registration. At the time of submitting this manuscript revision, patient recruitment is ongoing and has not been completed. Those enrolled participants had no history of chronic nausea and vomiting, no history of motion sickness, and no plan to use opioid drugs for analgesia within 24 h after surgery.

### Randomization and blinding

After informed consent is obtained, block randomization is employed. An independent administrator not involved in this study sets a block length of 4, generating a random sequence using the online Sealed Envelope tool. Participants are randomized in a 1:1 ratio to either the taVNS group or the sham group. During this process, allocation concealment is guaranteed by using sealed envelopes and the anesthesiologist responsible for the surgery has no a priori knowledge of the intervention assignment. The medical team providing care during the perioperative period, outcome assessors, investigators, and patients are also blinded to the group assignment. After the participant enters the operating room, an anesthesia assistant who is not involved in the data collection and outcome assessment opens the envelope in the absence of the anesthesiologist, assigns the patient to either the taVNS or the sham group, sets the vagus nerve electrical stimulation parameters, and places the vagus nerve electrical stimulation device into an opaque black bag. The anesthesiologist then performs anesthesia induction immediately. Due to the anterograde amnesic effect of anesthesia, the patient remains unaware of the intervention postoperatively. To ensure the effectiveness of patient blinding, a random selection of patients is surveyed before unblinding to determine which group they believed they had been assigned to. The proportion is then calculated, and if it is close to 1:1, it indicates successful blinding. Follow-up personnel and ward staff remain unaware of the group assignments. After statistical results are generated, unblinding is performed for all participants.

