### Data collection

Data will be collected using dedicated case report forms (CRFs) and managed in a secure electronic database. The demographic and baseline data include age, height, weight, BMI, ASA physical status, Apfel risk score, smoking status, history of motion sickness/PONV, comorbidities, and preoperative medications. Intraoperative data include anesthetic doses (propofol, remifentanil, volatile agents), vital signs at key time points, episodes of hypotension/bradycardia with interventions, surgical duration, fluid administration, and taVNS/Sham protocol details (group assignment, stimulation parameters, duration). Postoperative data include incidence of PONV assessed at 1 h after PACU arrival and 2, 6, 12, and 24 h postoperatively, nausea severity (11-point NRS) at the above time points, use and dose of rescue antiemetics within 24 h, and patient satisfaction (5-point Likert scale) at 24 h. Additional data collected include all adverse events (e.g. skin erythema, dizziness) with details on their nature, severity, and relationship to the intervention; heart rate variability; 24-hour postoperative opioid consumption; the total cumulative consumption of opioid analgesics; and blinding assessment (patient guess).

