Previous studies have shown that only mild and transient adverse events, such as erythema at the electrode site have been reported with taVNS [27]. In contrast, common antiemetic drugs are associated with side effects such as metoclopramide-induced oculogyric crisis [28], as well as potential sedation, headache, and QT interval prolongation linked to 5-HT3 receptor antagonists [29–31]. This highlights the potential advantage of taVNS in reducing polypharmacy and related drug side-effects. At present, no potential risks associated with left ear vagus nerve stimulation such as bradycardia and hypotension have been observed, likely due to the use of low-intensity transcutaneous auricular stimulation rather than invasive cervical vagus nerve stimulation. Additionally, theoretically, the right vagus nerve mainly controls the sinoatrial node [32]. Therefore, the possibility of experiencing bradycardia and hypotension due to stimulation of the right vagus nerve is greater. Furthermore, we collect patient-reported outcomes, including postoperative satisfaction. Exploratory analyses also detect the influence on opioid consumption of taVNS. These explorations require cautious interpretation, provide a more comprehensive assessment of the intervention’s utility and its impact from the patient’s perspective. Finally, preliminary subgroup analyses exploring whether the treatment effect is consistent across different ages or Apfel risk categories will need confirmation in future, larger trials.

This study is subject to several limitations. The findings of the single-center study require verification through multi-center studies with larger sample sizes. The relatively short follow-up period (24 h) may not fully capture late-onset PONV or potential sustained effects of taVNS. A single intraoperative stimulation may be insufficient, especially during prolonged surgeries, increasing the risk of a negative result. We plan subgroup analyses based on surgical duration. The results of this subgroup analysis may inform the design of future trials investigating optimized stimulation protocols. Despite the application of blinding, the distinct sensory perception induced by taVNS may compromise the blind in some patients or assessors. To verify the integrity of the blinding procedure, we will assess the final distribution of participants across study groups. A ratio close to 1:1 would provide indirect evidence of the validity of the outcome assessment under blinded conditions.

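### One fixed block length of 4 at a single site, disclosed while recruitment was open, would make a third of assignments predictable to anyone who knows the earlier ones; undisclosed varying block sizes are a cheap, modest improvement

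*Protocol article*

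**What the plan says.** All places are in the protocol article.

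- **Randomization and blinding** sets the method: "After informed consent is obtained, block randomization is employed", then "An independent administrator not involved in this study sets a block length of 4, generating a random sequence using the online Sealed Envelope tool", with "Participants are randomized in a 1:1 ratio to either the taVNS group or the sham group". No stratification factor is mentioned.
- **Study design and registration** makes it one site: "This study is a single-center, prospective, double-blinded, randomized and sham-controlled clinical trial".
- **Study population** gives the status at manuscript revision: "patient recruitment is ongoing and has not been completed".
- **Randomization and blinding** also describes who learns the assignment: "an anesthesia assistant who is not involved in the data collection and outcome assessment opens the envelope in the absence of the anesthesiologist". This happens once the patient has arrived for surgery. The same section says that sealed envelopes conceal the allocation and that the care team, assessors, investigators and patients are blinded.
- **Data collection** lists, among the intraoperative data, "taVNS/Sham protocol details (group assignment, stimulation parameters, duration" of treatment. It does not say who may see that field.
- **Discussion** concedes that "the distinct sensory perception induced by taVNS may compromise the blind in some patients or assessors".

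**The concern.** A sealed envelope hides the next assignment physically. It cannot hide what follows by deduction from the assignments already made. When every block has length 4 and holds two patients per arm, the fourth assignment in a block follows from the first three, and the third and fourth both follow when the first two match. With one list at one site, block boundaries are found by counting from the first patient. Concealment then depends on two things: nobody who influences patient selection knows the earlier assignments, or nobody knows the block length. The article has given up the second safeguard, at a time when some envelopes were still unused.

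What is at stake is selection before the envelope is opened: which patient is approached next, or the order of the day's list, which decides who receives the next envelope (assuming envelopes are used in sequence). The primary outcome is any nausea or vomiting within 24 h. A difference in baseline risk between the arms would pass straight into the relative risk, and the unadjusted chi-square test would not remove it.

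**Working it through.** The plan gives no predictability figure to reproduce. Its one computed design figure, 158 patients, is recovered as a check on the inputs. With the unpooled two-proportion formula, 40% against 20%, two-sided 0.05 (sidedness assumed) and power 0.80, n = (0.24 + 0.16) × (1.960 + 0.842)² / 0.20² = 78.5. That is 79 per arm and 158 in total. Nothing below changes this figure.

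**Inputs from the article:** block length 4, ratio 1:1, one site, target 100 per arm, control incidence 40%. **Inferred:** no stratification, because none is described.

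**Step 1. Certain predictions, fixed block of 4.** There are 6 equally likely orders of two and two.

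| Position in block | Probability that it is determined | Probability that the best guess is right |
|---|---|---|
| 1 | 0 | 1/2 |
| 2 | 0 | 2/3 |
| 3 | 1/3 (first two match) | 1/3 × 1 + 2/3 × 1/2 = 2/3 |
| 4 | 1 | 1 |

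The share known with certainty is (0 + 0 + 1/3 + 1)/4 = 1/3, or 200/3 ≈ 67 patients. The best guess is right in (1/2 + 2/3 + 2/3 + 1)/4 = 17/24 = 70.8%, against 50% by chance. Both figures assume that every earlier assignment is known in order.

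**Step 2. Varying block sizes.** 300 lists of 200 patients were simulated with sizes drawn at random from 4, 6 and 8. The observer knows every earlier assignment and the set of sizes, but not their order. Certain predictions are about 2% (about 4 of 200) and the best guess is right about 68% of the time. With sizes 4 and 6 only, the figures are about 5.5% and 69.3%.

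**Step 3. What this could do to the test.** The illustration assumes no true effect, a base risk of 40%, 100 per arm, and a baseline risk moved up or down by s according to the guessed arm. With g the probability of a correct guess, the expected spurious difference between arms is 2 × s × (2g − 1). The standard error is √(2 × 0.40 × 0.60 / 100) = 0.0693.

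For s = 0.05:
- Fixed blocks of 4: 2 × 0.05 × (2 × 0.708 − 1) = 4.2 points.
- Varying blocks (g ≈ 0.681): 2 × 0.05 × (2 × 0.681 − 1) = 3.6 points.

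Two-sided type I error, by normal approximation:

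| Assumed shift s | Fixed block of 4 | Varying 4/6/8 |
|---|---|---|
| 2.5 points | 6.0% | 5.8% |
| 5 points | 9.2% | 8.2% |
| 10 points | about 22% | about 18% |

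The shift s and full knowledge of earlier assignments are assumptions; the documents give neither. If no earlier assignment is known to anyone who selects or schedules patients, g = 0.5 and the bias is zero.

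**The case against.** The strongest reply is that the premise is not shown. The list comes from an independent administrator. The envelopes are opaque and sealed, and are opened only after consent, in the operating room and without the anesthesiologist. The device goes into an opaque bag, and the team and assessors are blinded. This stands: the article describes no route by which a recruiter or scheduler learns past assignments.

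The second reply is that the remedy does little to the illustrated harm. That also stands. Type I error in the illustration follows the best-guess rate, which falls only from 70.8% to about 68%. The large drop is in certain predictions.

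A reader might infer more than the documents support:

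- **That concealment has failed or the blind is broken.** No leak is documented. The assistant is expressly kept out of data collection and outcome assessment; the article's silence on screening or scheduling does not show that the assistant does either.
- **That listing group assignment among the collected data contradicts the blinding.** Recording the assignment is normal. Access to that field is detail that a condensed article may leave to the full protocol.
- **That the conceded sensory unblinding feeds prediction.** It concerns belief about a patient's own arm. Prediction would need assignments from the same block, in order, to reach whoever selects patients. Titration is also described for both groups, with stimulation only under anesthesia.
- **That predicted assignment biases anesthetic or analgesic exposure.** By then the envelope is open, and a leak would reveal the current assignment directly, whatever the block length.
- **That the article appeared while recruitment was open.** Only the status at revision is stated; no publication date is given.

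**Conclusion.** The point holds as a weakness of design, not as evidence of bias. A single known block length of 4 makes 1/3 of assignments certain to anyone holding the ordered history, and the article discloses that length. The one-third and 70.8% figures are exact under that condition. They rest on a single unstratified list, which is inferred from silence. The consequence for the primary comparison is conditional on a leak that the documents do not show, and on a shift in case mix whose size is assumed. Varying the block sizes removes nearly all certain predictions but leaves most of the illustrated inflation in place for a fully informed guesser. Severity is low; it is a cheap improvement worth making if envelopes remain unused.

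**What to change.** For envelopes not yet used, have the independent administrator generate a new sequence with randomly varying block sizes, for example 4, 6 and 8. The sizes should be kept from site staff until database lock, and the amendment should say only that they vary.

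Two sentences can be added as clarification. In Randomization and blinding: the person who opens envelopes takes no part in screening, consent or the ordering of the list. In Data collection: group assignment is held apart from forms that blinded staff see.

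The cost is a short amendment and re-stuffed envelopes, with the usual care needed when a list is replaced during recruitment. The arms may end slightly unequal: at most 4 patients from an unfinished block of 8, plus 2 if the change falls inside a block of 4. The loss of power is negligible, no patients are added, and the required 158 is unchanged.

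### The blinding survey asks only a random subset of patients and no assessor, although the Discussion concedes that assessors may be unblinded and appears to lean on a near-1:1 ratio to support outcome assessment

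*Protocol article*

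**What the plan says.** Four places in the protocol article bear on this.

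- **Randomization and blinding.** To check patient blinding, "a random selection of patients is surveyed before unblinding to determine which group they believed they had been assigned to". No sample size is given. The criterion follows: "The proportion is then calculated, and if it is close to 1:1, it indicates successful blinding". The same section says that outcome assessors, follow-up personnel and ward staff do not know the allocation, and that unblinding comes last: "After statistical results are generated, unblinding is performed for all participants".
- **Data collection.** The blinding item is the patient's guess. No assessor's guess is listed here or elsewhere.
- **Table 1.** Nausea, vomiting, NRS and adverse events are all scheduled at 1, 2, 6, 12 and 24 h, and the satisfaction scale at 24 h. There is no row for the guess.
- **Discussion, limitations.** The article concedes that "the distinct sensory perception induced by taVNS may compromise the blind in some patients or assessors". It then says that blinding integrity will be verified from how participants are finally distributed between the groups, and that a ratio near 1:1 "would provide indirect evidence of the validity of the outcome assessment under blinded conditions".

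**The concern.** The risk that the Discussion names and the check that is planned do not match. The risk covers patients and assessors; the check covers some patients. The primary endpoint counts any nausea or vomiting, and nausea is a subjective symptom elicited by active questioning at five time points, so the questioner's blind is relevant alongside the patient's. The Discussion itself calls successful blinding essential for the subjective outcomes.

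Two things are at stake. First, a small subset could return a ratio near 1:1 by chance when a real share of patients had identified their arm. Second, a reader of the final report could take that ratio as reassurance about assessors, on whom no guess was collected.

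**Working it through.** **What the plan fixes.** It gives no figure for the survey. Its total of 158 reproduces with the unpooled formula: (0.40×0.60 + 0.20×0.80) × (1.960 + 0.842)² / 0.20² = 78.5, so 79 per arm. This point does not depend on that figure. The only number used below is the recruitment target of 100 per group (Sample size).

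**Step 1: precision in one arm.** For a share of guesses near 0.5 among m patients surveyed per arm, the 95% half-width is 1.96 × √(0.25/m). For m = 20 this is 1.96 × √0.0125 = 0.219.

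**Step 2: power to see partial unblinding.** Suppose 65% guess correctly in both arms, so that 65% of the taVNS arm and 35% of the sham arm guess taVNS. For a two-sided 5% comparison of the arms, the mean share is 0.50 and

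power = Φ[(0.30 − 1.96 × √(2 × 0.25/m)) / √(2 × 0.65 × 0.35/m)].

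For m = 20: (0.30 − 1.96 × 0.1581) / 0.1508 = −0.066, and Φ(−0.066) = 0.474.

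| Surveyed per arm (assumed) | 95% half-width, one arm | Power at 65% correct in both arms |
|---|---|---|
| 10 | 31 points | 26% |
| 20 | 22 points | 47% |
| 30 | 18 points | 65% |
| 50 | 14 points | 86% |
| 100 (everyone) | 10 points | 99% |

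At 20 per arm and 70% correct in both arms, the same formula gives Φ(0.62), about 73%. Moderate unblinding would then often be missed, but it would not be undetectable.

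**Step 3: assessors.** No assessor's guess is recorded, so a survey of any size gives no direct information about their blind. Patients are under anesthesia during the 30 min of stimulation, so their guesses are a poor stand-in for those of the people who question them later.

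**Step 4: the Discussion sentence on either reading.** Its wording concerns the distribution of participants between groups and does not name the survey.

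- Read as the survey (the natural reading, since it repeats the near-1:1 criterion and claims to verify blinding), it rests on patients' guesses and does not reach assessors.
- Read as the allocation ratio, it describes the result of 1:1 block randomization, which is near 1:1 whether or not anyone is blinded.

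Neither reading supports a statement about outcome assessment.

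**The case against.** The case for the plan is considerable, and much of it stands.

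- **Stated purpose.** The blinding section limits the survey to patient blinding. Its link to outcome assessment comes from the Discussion, is partly a matter of interpretation, and is offered only as indirect evidence. This stands; hence *appears to lean on* is as far as the text goes.
- **Article-level detail.** The exact time of the survey and a row in Table 1 may sit in the full protocol. A reader might infer from "After statistical results are generated, unblinding is performed for all participants" that guesses could be taken long after discharge. The article does not say so, and timing alone is no finding. The random subset and the patient-only guess, by contrast, are choices that the article states.
- **Unknown size.** Without a subset size, imprecision is possible rather than shown; at 50 per arm the survey would be fairly informative.
- **Erythema.** A reader might infer that assessors will recognize taVNS patients by a mark on the ear, because "erythema at the electrode site have been reported with taVNS" and adverse events share visits with nausea. The documents do not support that. Erythema is given as one example of mild, transient events; electrodes are placed in both arms, and the threshold titration is described before the arms diverge; no rate by arm is given; and nothing says that the person asking about nausea inspects the ear.
- **Procedural masking.** A separate assistant sets the device, which goes into an opaque bag, and follow-up staff are not told the allocation. An assessor's guess adds a check on this and does not replace it. But the article itself lists assessors among those who may be unblinded, so a direct check answers a risk that it raises.

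**Conclusion.** The concern holds as a modest improvement to the design. The plan samples patients when all of them are already seen at 24 h, collects nothing on assessors, and includes a Discussion statement that its data could not support on either reading. The cost in precision depends on an unstated subset size: at an assumed 20 per arm, a half-width of about 22 points and 47% power, against about 10 points and 99% if all 100 per arm answer. The power figures assume the same share of correct guesses in both arms and a two-sided 5% test.

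A reader might go further and infer that the assessors' blind has failed or that the primary comparison is biased. The documents show neither. The sample size, the primary analysis and the masking procedure are unaffected.

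**What to change.** 1. Ask every patient for the allocation guess at the existing 24 h visit, after the last nausea, vomiting, NRS and satisfaction item.
2. Have the outcome assessor record their own guess at that visit.
3. Report guesses by arm, separately for patients and assessors. A pooled ratio is not enough: with 100 per arm and 70% correct in each, 70 + 30 = 100 guess taVNS and 100 guess sham.
4. Limit the Discussion statement to what these data show about each group.
5. As a precaution, complete the nausea, vomiting and NRS items before any adverse-event check at each visit.

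The cost is small: asking the existing patient item of everyone, one added assessor item, and an instruction on order, with no new visit and no change in sample size. There are two downsides. Guesses made after the outcomes can be influenced by whether the patient had PONV, so an effective treatment could look like a broken blind; they should be interpreted with the outcome in mind, for example by also showing them by PONV status within arm. And because recruitment has begun, patients already past 24 h cannot be asked on this schedule; the report should state how many were not.

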### Sample size

The sample size was calculated with the PASS 15.0 software. It is reported the incidence of PONV among Chinese patients undergoing elective gynecological laparoscopic surgery is approximately 40% following dual-agent prophylaxis with dexamethasone and ondansetron [5]. Based on previous studies, we assume that the incidence of PONV in the taVNS group would be reduced to 20%[22,23]. To provide a significance level of 0.05 and a power of 0.8, a sample size of 158 patients will be required. Considering potential protocol deviations and withdrawal of consent, the recruitment target will be increased to 100 patients in each group.

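### The stated test of blinding (a ratio close to 1:1) cannot tell a broken blind from an intact one; guesses should be compared with actual allocation, arm by arm

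*Protocol article*

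**What the plan says.** Under Randomization and blinding, the article describes the patient survey: "a random selection of patients is surveyed before unblinding to determine which group they believed they had been assigned to". The criterion follows at once: "The proportion is then calculated, and if it is close to 1:1, it indicates successful blinding". The size of the sample and the meaning of close are not stated.

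The limitations paragraph of the Discussion describes the check differently: "we will assess the final distribution of participants across study groups". It then draws the inference: "A ratio close to 1:1 would provide indirect evidence of the validity of the outcome assessment under blinded conditions".

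Three other statements matter here. Allocation is equal: "Participants are randomized in a 1:1 ratio to either the taVNS group or the sham group". The administrator "sets a block length of 4", and under Sample size "the recruitment target will be increased to 100 patients in each group". The Data collection section lists both the patient's guess and the group assignment among the recorded items, but no section combines them into a measure of blinding.

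**The concern.** A test of blinding has to ask whether patients' guesses agree with the arm they were really in. The rule under Randomization and blinding refers only to which group patients believed they were in, and nothing in it brings in the true arm. With equal allocation, a ratio of guesses near 1:1 is what one expects both when nobody knows and when everybody knows. The Discussion version does not involve guesses at all: it looks at group sizes, which the randomization sets.

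This matters because any episode of self-reported nausea counts toward the primary endpoint. The Discussion also says that blinding is central to limiting bias in subjective outcomes, and concedes that sensation from the device might unblind some patients or assessors. A check that passes in either case would lend support to the main result that it has not earned.

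**Working it through.** The article gives no figure for this rule beyond close to 1:1, so there is nothing to reproduce. The check is what the rule returns under known guessing patterns.

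**Inputs from the article.** Allocation 1:1, blocks of 4 (Randomization and blinding); 100 per arm (Sample size).

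**Assumptions, because the article does not give them.** Survey size m between 20 and 100; close to 1:1 means that 40–60% of those surveyed guess taVNS; no don't-know answers.

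**Step 1: expected split.** Let a be the share of the taVNS arm guessing taVNS and b the share of the sham arm guessing taVNS. Per 100 patients in each arm:
- taVNS guesses = 100a + 100b; sham guesses = 200 − that number
- overall share correct = (a + 1 − b)/2
- index, taVNS arm = 2a − 1; index, sham arm = 2(1 − b) − 1

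| Pattern | a | b | taVNS : sham guesses | Rule | Share correct | Index taVNS / sham |
|---|---|---|---|---|---|---|
| All correct | 1 | 0 | 100:100 | pass | 100% | +1 / +1 |
| 75% correct in each arm | 0.75 | 0.25 | 100:100 | pass | 75% | +0.5 / +0.5 |
| Random guessing | 0.5 | 0.5 | 100:100 | pass | 50% | 0 / 0 |
| All wrong | 0 | 1 | 100:100 | pass | 0% | −1 / −1 |
| 80% of each arm guess taVNS | 0.8 | 0.8 | 160:40 | fail | 50% | +0.6 / −0.6 |

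The first four patterns run from complete unblinding to complete error, and the rule treats them alike. In the fifth, the guess says nothing about the arm, yet the rule reports failure. The per-arm index separates all five. These counts are expectations for the whole trial; a surveyed subset varies around them, which is the next step.

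**Step 2: chance of passing in a random subset of m patients.** If every patient guesses correctly, the number X guessing taVNS equals the number of taVNS patients drawn, so X is hypergeometric (200 patients, 100 taVNS, m drawn). Under random guessing, X is binomial (m, 0.5). The chance of passing is P(0.40 ≤ X/m ≤ 0.60).

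| m surveyed | Every guess correct | Random guessing |
|---|---|---|
| 20 | 76% | 74% |
| 40 | 89% | 85% |
| 50 | 93% | 88% |
| 60 | 96% | 91% |
| 100 | 99.7% | 96% |

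The broken blind passes slightly more often because sampling without replacement from a balanced trial reduces the variance: m/4 × (200 − m)/199, against m/4 for random guessing. At m = 50 this is 12.5 × 150/199 = 9.4 against 12.5. With a stricter band of 45–55%, the figures are 52% against 50% at m = 20 and 88% against 73% at m = 100, so the ordering does not depend on the 40–60% choice.

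**Step 3: the Discussion version.** With 200 patients in blocks of 4 there are 200/4 = 50 blocks, each 2:2, giving 100:100. At any point in the sequence the arms differ by at most 2. Knowledge of allocation does not enter this ratio.

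**The case against.** **The proportion could mean correct to incorrect guesses.** This is a fair point, because the article does not define the term. On that reading all-correct guessing gives 200:0 across the whole trial and fails, as it should. But the text does not say this: the proportion follows directly on the group patients believed they were in, and the Discussion wording has no element of correctness. Pooling across arms would also still hide differences between them, since random guessing and the 80% pattern both give 100 correct to 100 incorrect, although their per-arm indices are 0/0 and +0.6/−0.6.

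**The Discussion sentence may be a loose restatement of the survey.** Possibly so. It is then a wording error rather than a second test, but as printed it names a quantity that cannot reflect blinding, and it needs correcting either way.

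**Complete unblinding is an extreme case.** This stands. The Study intervention section describes the same threshold titration in both arms before induction, with the arms differing only once the patient is anesthetized, so the real risk to patient blinding may be modest. The complaint is that the check could not show this, not that the blind is likely to fail.

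**A reader might infer that the double-blind claim cannot be verified at all.** The documents do not support that. It is true of the rule, not of the data: guess and assignment are both recorded, so the right table can be built for those surveyed.

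**Details may sit in the full protocol or analysis plan.** That covers survey size, timing and response options. It does not cover a criterion and an interpretation that the article states outright.

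**Conclusion.** The criterion is wrong as written, not merely short of detail. On its literal reading it gives the same expected result for a fully broken blind and an intact one, and it rejects a harmless lopsided pattern. That conclusion needs only 1:1 allocation. The pass probabilities (about 76% to 99.7% when every guess is correct, about 74% to 96% under random guessing) rest on the assumed survey size and the assumed 40–60% band. The Discussion version is uninformative by design.

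The consequence is limited. The check does not enter the primary comparison, the analysis populations, the multiplicity rule or the sample size, and the concealment and masking procedures do not depend on it. A reader might go further and conclude that the trial is unblinded or its primary result unreliable; nothing in the article shows that. What is at stake is whether the trial's own statement about blinding of a self-reported endpoint will be valid.

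**What to change.** 1. Under Randomization and blinding, replace the 1:1 criterion with a table of guess (taVNS, sham, don't know) against actual allocation. Report a blinding index for each arm (for example Bang's: correct minus incorrect guesses, divided by all respondents in that arm) with its 95% CI. Values near 0 in both arms, or roughly equal and opposite, indicate that guesses carry little information about the arm. Record the guesses before allocation is revealed.
2. In the Discussion, replace the sentences on the distribution of participants across groups with a reference to this analysis.
3. Optional, where feasible for patients still to be enrolled: ask every patient at one fixed time, and ask the outcome assessor for a guess as well, since the article names assessors as possibly unblinded but lists only the patient's guess.

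Items 1 and 2 cost wording and one table; for patients already surveyed they use data the article says are collected, although a don't-know category may be available only from now on. Item 3 costs one question per patient and per assessor. Recruitment is under way, so it cannot be applied on schedule to patients already past their 24 h close-out. The Data collection section does not restrict the patient guess to a subset, so the sponsor should first check whether it is already recorded for everyone.
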